#### **27c. Assumptions checks for statistical methods.**

Not relevant.

#### **27d. Alternative methods if assumptions are violated.**

For comparisons of binary obstetric complications and perinatal outcomes, we will use Fisher's exact test, instead of the Chi-square test, if the number of events is ≤ 10.

#### **27e. Planned sensitivity analyses**

Not relevant.

#### **27f. Planned subgroup analyses and definitions**

Raw count data describing the distribution of reproductive outcomes per study group (A, B, C and D) will be presented in Supplementary files. Comparisons of reproductive outcomes between separate study groups will not be conducted.

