## Section 3: Study Methods

### 9. Trial Design

Randomised, single-blinded, controlled, trial using a 2 x 2 factorial design.

Participants will be randomised 1:1:1:1 to the following four study groups:

A) Luteal phase progesterone and warming+transfer 6 days after hCG trigger

B) Luteal phase progesterone and warming+transfer 7 days after hCG trigger

C) No luteal phase progesterone and warming+transfer 6 days after hCG trigger

D) No luteal phase progesterone and warming+transfer 7 days after hCG trigger.

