## 11. Sample Size

“A total of 604 patients are required to have an 80% chance of detecting, at a significance level of 5%, an increase in live birth rate to 31% in the intervention group from 21% in the control group. Sample size calculation does not need correction for the two interventions, as they are considered fully independent of each other.”[1]

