## 12. Framework

The study is designed as a superiority trial making the following comparisons:

Comparison I: Vaginal progesterone (group A+B) vs no vaginal progesterone (groups C+D).

Comparison II: Blastocyst warming+transfer day 6 after hCG trigger (group A+C) vs blastocyst warming+transfer day 7 after hCG trigger (group B+D).

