## Section 4: Statistical Principles

### Confidence Intervals and P-Values

#### 16. Level of statistical significance to be used.

A significance level of 5% will be used.

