### 27b. Adjustments for covariates.

The multivariable regression analyses will be adjusted for the stratification variables (trial site, female age <37 or ≥37 years, number of previous oocyte retrievals, number of previous FET cycles, blastocyst expansion grade at the day of embryo freezing) in addition to parity and day of blastocyst vitrification.[4]

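### The SAP analyses a 2×2 factorial trial only through two pooled comparisons and pre-specifies no estimate of the interaction between progesterone and transfer day.

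*SAP*

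**What the plan says.** Section 9 describes the design: "Randomised, single-blinded, controlled, trial using a 2 x 2 factorial design". It continues: "Participants will be randomised 1:1:1:1 to the following four study groups". Groups A and B receive luteal progesterone and C and D do not. Transfer is on day hCG+6 in A and C, and on day hCG+7 in B and D.

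Section 12 defines two comparisons only, A+B against C+D for progesterone and A+C against B+D for transfer day. Section 11 sizes the trial at 604 women for 31% against 21% live births and makes no correction for having two interventions, "as they are considered fully independent of each other".

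Section 27f places raw counts for the four groups in supplementary files and then states: "Comparisons of reproductive outcomes between separate study groups will not be conducted". Sections 27c (assumption checks) and 27e (sensitivity analyses) are both marked not relevant.

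Section 27b begins: "The multivariable regression analyses will be adjusted for the stratification variables". It then adds parity and day of vitrification. Neither the other randomised intervention nor a product term is listed. The SAP does not mention interaction anywhere.

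**The concern.** In a factorial trial, each pooled contrast averages the effect of one intervention over the two levels of the other. The average describes both levels well if the two effects are roughly additive on the scale used. Randomisation makes the two allocations independent, but it does not make the effects independent. Here both factors concern the same process, as the trial's title says: preparing and timing the endometrium. An interaction is therefore plausible, though nothing in the SAP shows that one is likely.

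What is at stake is interpretation. If progesterone helped on one transfer day and not on the other, the pooled result would be an average that matches neither day. The authors would have published the four sets of counts with no pre-specified contrast, scale or rule for reading them. Read literally, the last sentence of section 27f also rules out the interaction contrast and the within-level effects, since each compares groups A to D.

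**Working it through.** **Inputs.** From section 11: 604 women, 21% and 31%, 80% power. From section 16: "A significance level of 5% will be used" (two-sided is assumed here because it reproduces the sample size). From section 9: equal allocation, hence 604/4 = 151 per group and 302 per side of each pooled comparison. The average rate is (21% + 31%)/2 = 26%. The group rates in steps 3 and 5 are illustrative assumptions.

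**1. The SAP's own figure.** With pooled variance and no continuity correction,

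n = [1.96·√(2·0.26·0.74) + 0.842·√(0.21·0.79 + 0.31·0.69)]² / 0.10² = 301 per side, or 602 in total.

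This agrees with 604. Power at 302 per side is 80.2%. The sample size is right for one pooled comparison.

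**2. Precision of the interaction.** The contrast is (A−C)−(B−D) in live birth proportions.

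- SE = √(4·0.26·0.74/151) = 0.0714, or 7.1 points. A pooled effect has SE √(2·0.26·0.74/302) = 0.0357, half as large.
- 95% CI half-width = 1.96 × 7.14 = 14.0 points.
- Interaction detectable with 80% power = (1.96 + 0.842) × 7.14 = 20.0 points.
- Power for a 10-point interaction: 10/7.14 = 1.40, and Φ(1.40 − 1.96) ≈ 29%.
- Powering for a 10-point interaction would need about 2,420 women.

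**3. Two illustrations.**

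| Assumed rates | Progesterone effect, day 6 / day 7 | Pooled effect | Interaction | Power to detect the interaction |
|---|---|---|---|---|
| A 26%, C 26%, B 31%, D 21% | 0 / +10 | 28.5% − 23.5% = +5 | −10 | about 29% |
| A 21%, C 31%, B 31%, D 21% | −10 / +10 | 26% − 26% = 0 | −20 | about 80% |

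In the second case the pooled comparison has a true difference of zero, while the contrast that the SAP leaves out would probably reveal the reversal. In the first case the interaction estimate would usually be inconclusive.

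**4. Within-level effects.** Each compares 151 with 151: SE = √(2·0.26·0.74/151) = 0.0505, so the 95% CI is about ±9.9 points.

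**5. Cell-versus-cell tests.** A test of 21% against 31% with 151 per group has about 51% power.

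**The case against.** The case for leaving the SAP alone has several sound parts.

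- **The pooled questions are the trial's questions.** Sections 8 and 12 ask about progesterone and transfer day overall. Under equal allocation each pooled contrast validly estimates an average effect, with or without interaction. A reader might infer that the primary comparisons are invalid unless independence is proved. The SAP does not support that; interaction limits how far the average carries to each day.
- **The bar on cell comparisons is defensible.** Such tests have about 51% power for the planned difference, and section 17 plans no multiplicity adjustment. Ruling them out in advance limits selective reporting.
- **The counts will be published.** A reader might infer that an interaction could never be seen. In fact a crude interaction and its standard error can be computed from the counts in section 27f. It would be post hoc and unadjusted, with no agreed reading.
- **Lost power is not a cost of the omission.** In the first illustration the pooled test has about 29% power instead of 80%. That follows from an average effect of 5 points, and a uniform 5-point effect giving the same pooled rates would have the same power. Estimating the interaction restores none of it.
- **The missing covariate does little harm.** With equal allocation the two factors are nearly orthogonal, so any bias in the pooled risk difference should be small. Section 27b omits the other factor but does not expressly exclude it.
- **The independence statement is about sample size.** It is quoted from the protocol, where more justification may stand.

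All of this narrows the point. None of it supplies a planned estimate of interaction.

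**Conclusion.** The point holds in a limited form. The SAP pre-specifies no estimate of whether each pooled effect applies at both levels of the other intervention, and section 27f confines group-level results to uncompared counts. The primary comparisons and the sample size stand.

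The gain from a planned estimate is modest. It could reveal a reversal of about 20 points, but it could not exclude a moderate interaction, since its interval is about ±14 points. Leaving the other intervention out of section 27b is a minor matter in the per-transfer and intention-to-treat sets. It is more relevant in the per-protocol and as-treated sets of section 20, where balance between groups can be lost. Section 19a expects some transfers to move off the allocated day.

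The figures assume that all 604 women are analysed in four equal groups, with an average live birth rate of 26%. The primary set contains only women who undergo transfer, so fewer than 604 would be analysed if some randomised women have no transfer, and precision would then be somewhat lower.

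**What to change.** In section 27f, keep the pooled comparisons primary and limit the closing sentence to cell-versus-cell significance tests, so that it does not contradict the addition. Then add:

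> *The interaction (A−C)−(B−D) in live birth will be estimated on the risk-difference scale with a 95% CI, and the effect of each intervention will be shown with a 95% CI within each level of the other. These are descriptive estimates that qualify interpretation and are not a gate.*

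The risk-difference scale is the one already chosen in sections 18 and 27a.

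In section 27b, add the other allocated intervention to the adjusted models.

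The cost is one model term and one table, with no change to the sample size or the primary comparisons. The drawback is low precision. The text should give the ±14-point half-width, so that an interval covering zero is not read as evidence that the interventions act independently.

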### **28. Missing Data**

For transparency, rates will be presented as a fraction (e.g. n events/n individuals in study group) and percentage.

### **29. Additional Analyses**

Analyses on the association between the level of reproductive hormones on the day on ovulation trigger and on the day of blastocyst transfer with reproductive outcomes will be performed and published in separate publications. Analyses and outcomes described in said paper(-s) will not be further described in this statistical analysis plan.

Analyses on the self-reported health and wellbeing of women participating in the clinical trial and use of luteal phase progesterone support will also be conducted. Analyses and outcomes described in said paper(-s) will not be further described in this statistical analysis plan.

### **30. Harms**

Progesterone is routinely used for patients undergoing ovarian stimulation and embryo transfer and is not expected to cause harm to participants. The timing of embryo transfer will not cause any harm to the patients. Apart from extra study visits and blood samples, this study will cause very modest harm to participants.

In case of adverse reactions (AR), serious adverse events (SAEs), serious adverse reactions (SARs) and suspected unexpected serious adverse reactions (SUSARs) these will be registered

by allocated study staff according to study protocol. Data on patient safety and potential SAEs, SARs and SUSARs will be reported to the Danish Medicines agency annually according to Danish law.

Should patients participating in the trial give birth to children with congenital malformations or in the rare event of perinatal death, these outcomes will be publicly disseminated under “perinatal outcomes”, including comparisons of these outcomes across study groups.

## Statistical Software

### 31. Details on statistical packages

R Studio will be used to conduct the statistical analyses.

